## 1.2 SCHEMATIC DIAGRAM

[figure not shown]

**Schedule of enrollment intervention and assessments.** CI or SIs must obtain written consent by the screening test. The maximum screening period (from consent acquisition to registration / randomization) is 3 days. CI or SIs must start protocol treatment within 4 days of obtaining consent. Predetermined observations, investigations, and tests must be performed prior to administration of the study drug. If the decision to terminate the pregnancy is made before the protocol treatment is completed, the protocol treatment must be terminated at that point, and the patient shifts to the post-pregnancy observation period after delivery.

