**Table 1.3-1 Schedule of data collection and monitoring for participant (mother and fetus)**

| Period                                                               | Screening period a |                       | Observation period during pregnancy b |                                       |                            |                            |                            |                            |                            |                                          | Observation period after the termination of pregnancy  |                                                    | At the cancellation of the participation in the trial d | Follow-up observation after the cancellation of participation in the trial e |
|----------------------------------------------------------------------|-------------------------------|-----------------------|--------------------------------------------------|---------------------------------------|----------------------------|----------------------------|----------------------------|----------------------------|----------------------------|------------------------------------------|--------------------------------------------------------|----------------------------------------------------|--------------------------------------------------------------------|-----------------------------------------------------------------------------------------|
| Working item                                                         | Screening period Days -3 to 0 | Registration on Day 0 | Week 1 Day 1                                     | Week 2 Day 8 $\pm$ 2 day  | Week 3 Day 15 $\pm$ 2 days | Week 4 Day 22 $\pm$ 2 days | Week 5 Day 29 $\pm$ 2 days | Week 6 Day 36 $\pm$ 2 days | Week 7 Day 43 $\pm$ 2 days | Week 8~ c Day 50 $\pm$ 2 days | At the termination of pregnancy (delivery) $\pm$ 1 day | At examination for maternal discharge $\pm$ 2 days |                                                                    |                                                                                         |

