f. CI or SI must obtain consent before starting examination during the screening period.

g. CI or SI should care for patients in hospital at least for the period from the start of protocol treatment to 3 days after delivery.

- h. CI or SI must start protocol treatment within 4 days after obtaining consent.
- i. CI or SI should examine the estimated fetal weight once a week at or after Week 3, until the decision to terminate the pregnancy. However, the hematological examination and blood biochemical test should be performed only when needed at or after Week 4, until the decision to terminate the pregnancy.
- j. CI or SI should not take biological specimens from patients if the patients become complicated with COVID-19 infection. In addition, all preserved specimens should be abandoned.
- k. If CI or SI decides to cancel participation in the trial due to the adverse events, CI or SI should continue the investigation of adverse events due to the test drugs or drugs used concomitantly which are the reasons for the cancelation of participation in the trial, from the cancelation to the one-month postpartum medical examination.
- l. CI or SI should investigate the occurrence of adverse events in the subject (mother and fetus). As for the mother, CI or SI should investigate from the starting day of protocol treatment to the observation period after the termination of pregnancy (or day of cancelation of participation in the trial). As for the fetus, CI or SI should investigate from the starting day of protocol treatment to the termination of pregnancy (or day of cancelation of participation in the trial). However, if CI or SI decides to cancel participation in the trial due to the appearance of adverse events, CI or SI should continue the investigation of adverse events due to the test drugs or drugs used concomitantly which are the reasons for the cancelation of participation in the trial, from the cancelation to the one-month postpartum medical examination.
- m. CI or SI should investigate the decision day of the termination of pregnancy, the time (day, hour, minute) of delivery, the reasons for termination of the pregnancy (both maternal and fetal causes).
- n. CI or SI should investigate the delivery mode, presence/absence of stillbirth and the day of stillbirth, placental weight, and presence/absence of placental infarction.

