## **4 STUDY DESIGN**

### **4.1 STUDY DESIGN**

To compare the efficacy and safety of AZM and EM in combination with ABPC/SBT for the prevention of BPD in infants born to pregnant women with pPROM occurring at <28 weeks of

gestation, we will plan a phase II, multicenter, open-label, randomized, parallel-group study. The efficacy of AZM and EM will be evaluated by comparing the rate of events, with events defined as BPD36 of moderate or greater and infant death up to 36 weeks PMA. Safety will be evaluated by the occurrence of adverse events and side effects in mother and child.

The study is a clinical trial conducted during the hospitalization period for pregnant women admitted after the onset of pPROM and consists of a screening phase, a treatment observation phase from the date of protocol treatment initiation to termination of pregnancy, and a post-termination observation phase from termination of pregnancy to the date of discharge of the child.

The chief investigator (CI) or sub-investigator (SI) will screen and assess eligibility after obtaining consent. The CI or SI will enroll subjects in REDCap prior to the start of protocol treatment. After enrollment, eligible subjects will be assigned to the intervention or control group by stratified allocation. The screening period from obtaining consent to randomization will be a maximum of 3 days.

The CI or SI will initiate protocol treatment within 4 days of obtaining consent. The study drug Zithromax 500 mg for intravenous infusion or Erythrosine 500 mg for intravenous infusion will be administered under inpatient supervision with the start date as Day 1.

The protocol treatment period is 14 days from Day 1 to Day 14. If a decision of termination of pregnancy is made\*1 before completing the 14 days of dosing, the protocol treatment will be discontinued at that time.

From the end of protocol treatment until “date of birth”\*2, the prescribed observations, investigations, and tests are performed under inpatient supervision.

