The median number of weeks of gestational duration for pregnant women with pPROM is 2 weeks. Based on the annual number of deliveries, the number of births by week, and the percentage of pPROM, we can estimate that 1,200 newborns per year are born at <30 weeks to pregnant women with pPROM complications. In the 20 regional and comprehensive perinatal centers scheduled to participate in this study, the number of cases is estimated to be approximately 200 per year over a 2-year period. Assuming that 50% of the patients meet the eligibility criteria for this study and consent is obtained, 100 patients can be enrolled over a two-year period, and from the viewpoint of feasibility, the target number of cases for this study was set at 100. Under a two-tailed test and a significance level of 5%, the power of detection ranged from 0.516 to 0.995 when the assumed BPD36 incidence rate in the intervention group was 18.0% to 40.0%, which is considered to guarantee a power of at least 0.5.

For reference, the power curve for the BPD36 incidence rates of 18.0% to 60.0% in the intervention group are shown below. In addition, the incidence rates in previous foreign and domestic studies and the study at Saga Hospital are indicated by red lines.

[figure not shown]

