### **7.2 CONSENT TO PARTICIPATE**

After explaining the study subject in accordance with the method for obtaining consent, the fact that the explanation was given and the fact that consent was obtained should be noted in the medical record. If the subject does not consent on the date of explanation, but confirms his/her willingness to consent at a later date, the date of explanation and the physician's signature should be written on the consent form, which should be provided to the study subject together with the explanation. If the date of explanation and the date of consent are on the same day, record that the consent was given after sufficient time was given for consideration of participation in the study.

Screening may be performed on the same day after consent is obtained. If screening is not conducted on the same day, screening should be conducted within 3 days of the date of consent.

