## 10 CANCELTION AND COMPLETION

### 10.1 CANCELTION OF PARTICIPATION IN THE TRIAL

If the subject fails to comply with all study schedules, including efficacy and safety assessments, as well as discontinues protocol treatment for the following reasons (1. to 3.), participation in this trial should be canceled. This situation is called “cancellation of participation in the trial”.

If the protocol treatment is canceled before it has actually started, no observations should be performed, and appropriate treatment should be given so that the subject is not disadvantaged in

normal practice.

1. When the subject withdraws consent to participate in the study.
2. When “disease, etc.” that may lead to death or death occurs.
3. In addition, when the investigator determines that the risk of participating in the trial outweighs the benefits.

Basis for setting

- 1: Set from an ethical point of view.
- 2 – 3: Established from the viewpoint of subject safety.

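### The prose allows randomisation up to 4 days before the first dose, while the schedule tables show 1 day; the longer gap adds post-randomisation loss with the arm known

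*Protocol*

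**What the plan says.** **Limits in the prose.** Section 1.2 says "CI or SIs must start protocol treatment within 4 days of obtaining consent". Note h, attached to the protocol-treatment row of Table 1.3-1, repeats it: "CI or SI must start protocol treatment within 4 days after obtaining consent". Section 4.1 adds "The screening period from obtaining consent to randomization will be a maximum of 3 days". The prose links enrolment to dosing only by order: "The CI or SI will enroll subjects in REDCap prior to the start of protocol treatment" (section 4.1). Section 7.2 allows quick screening: "Screening may be performed on the same day after consent is obtained". Notes o to q of Table 1.3-1 also let recent pre-consent weight, blood, urine, ECG and ultrasound results stand in for screening tests.

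**Schedule.** Tables 1.3-1 and 7.5-1 head the randomisation column "Registration on Day 0", and section 6.2.1 defines Day 1 as the day of the first study infusion of either macrolide. Section 1.3 says that the study follows the table.

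**Women never dosed.** Section 7.4 has REDCap display the assigned group. Section 10.1 says "If the protocol treatment is canceled before it has actually started, no observations should be performed". Section 14.1 removes never-treated subjects from the FAS, hence from the PPS, which is drawn from it; the safety population holds treated subjects only.

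**The concern.** The prose and the schedule allow different intervals between randomisation and first dose. A site that follows the mandatory sentences has no stated reason to read the table's column heading as a limit. The prose also works the wrong way round: the faster the screening, the longer the permitted wait after allocation.

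The interval matters because the trial is open-label and the comparison is effectively among dosed women. Delivery, withdrawal or a change of mind between allocation and first dose takes a randomised woman out of the analysis after her arm is known. The FAS rule in section 14.2.2 that counts a missing primary outcome as an event cannot reach her, because she is not in the FAS. If such losses differ by arm, or are related to early delivery, the randomised comparison is disturbed.

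**Working it through.** **1. The permitted gap.** Count consent as day 0. Randomisation is on day r, with r between 0 and 3 (section 4.1; r = 0 is possible under section 7.2). The first dose is no later than day 4 (section 1.2, note h). The longest gap under the prose is 4 − r:

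| r | Longest gap (days) |
|---|---|
| 0 | 4 |
| 1 | 3 |
| 2 | 2 |
| 3 | 1 |

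Under the schedule tables the gap is Day 1 − Day 0 = 1 day. The two agree only when the full 3-day screening period is used (3 + 1 = 4).

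**2. The plan's own power.** Inputs from section 5.2: 50 per arm, control rate 60%, intervention rate 18% to 40%, two-sided 5%. For the two-proportion test with pooled null variance,

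z = [d√n − 1.96√(2p̄(1−p̄))] / √(p₁q₁ + p₂q₂).

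- 60% v 40%: (0.2 × 7.0711 − 1.96 × 0.7071) / 0.6928 = 0.041, power 0.516.
- 60% v 18%: (0.42 × 7.0711 − 1.96 × 0.6898) / 0.6226 = 2.599, power 0.995.

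Both match section 5.2.2.

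**3. Illustrative loss.** Section 5.2.2 says "The median number of weeks of gestational duration for pregnant women with pPROM is 2 weeks". Assuming a constant delivery hazard with that median, running from randomisation, the fraction delivered by t days is 1 − 2^(−t/14): 4.8%, 9.4%, 13.8% and 18.0% for t = 1, 2, 3 and 4.

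- 1-day gap: n = 50 × (1 − 0.048) = 47.6 dosed per arm; power at 60% v 40% is 0.496.
- 4-day gap used by every woman: n = 50 × (1 − 0.180) = 41.0; power 0.440.

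**4. Loss without a hazard model.** The Protocol does not say how many women will go undosed. If k per arm are dropped:

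| k per arm | Power, 60% v 40% | Power, 60% v 18% |
|---|---|---|
| 1 | 0.508 | 0.995 |
| 3 | 0.491 | 0.993 |
| 5 | 0.475 | 0.991 |

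**5. Selection.** Suppose there is no true effect, with 30 events in 50 in each arm, and k undosed women who would all have had events are lost from one arm only. That arm's rate becomes (30 − k)/(50 − k):

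- k = 1: 29/49 = 59.2%, a spurious difference of −0.8 points.
- k = 3: 27/47 = 57.4%, −2.6 points.
- k = 5: 25/45 = 55.6%, −4.4 points.

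**The case against.** The strongest reply is that the schedule already fixes the interval. Section 1.3 makes the table operative, the table says Day 0, section 6.2.1 says Day 1, and 3 days of screening plus 1 day gives the 4-day limit. That stands to this extent: a reader might infer that nothing in the Protocol connects randomisation to the first dose, and the tables show otherwise. It does not remove the mismatch, because the mandatory sentences and the table's own note h run from consent and permit more. The diagrams in section 1.2 and Figure 4.1-1 are not available here, so they cannot settle it; the text beneath them repeats the consent-based limits.

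Four other readings go further than the documents:

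- **That the woman waits untreated.** Sections 6.2.1 and 6.4.2 permit ABPC or ABPC/SBT infusion between consent and the start of protocol treatment.
- **That delivery before dosing plainly ends observation.** This is an inference. Section 10.1 does not list delivery among its reasons for cancelling participation. Section 6.2.6 treats a determined delivery as a reason to stop protocol treatment with observation continuing, but does not expressly address women never dosed.
- **That only a short gap can prevent the loss.** Continuing to observe every randomised woman (section 10.1) and retaining her in the analysis (section 14.1) would also address it.
- **That power falls to 0.44.** This needs every woman to be randomised on the consent day and to wait all 4 days, against the tables. The constant hazard is an assumption, and exclusion criteria 6 and 7 remove women for whom imminent termination of pregnancy is considered, so early delivery is probably overstated.

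**Conclusion.** The point holds as an inconsistency with a consequence. The prose permits a gap of up to 4 days between open allocation and first dose; the schedule shows 1 day. Each extra day gives more opportunity for a randomised woman to leave the analysis with her arm known.

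The main issue is possible selection after randomisation. Its size cannot be derived from the Protocol; the illustration gives spurious differences of about 1 to 4 points for 1 to 5 one-sided losses. The power effect is small: 0.516 to about 0.50 at 60% v 40% with the scheduled 1-day gap, and negligible at 60% v 18% for 1 to 5 losses per arm. Even the 1-day figure, 0.496, lies marginally under the floor of 0.5 claimed in section 5.2.2. The 0.44 is an upper-end illustration resting on the constant hazard, the 2-week median applied from randomisation, and universal use of the full gap.

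The exclusion of undosed women is a problem at any gap. The loose timing rule makes it larger.

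**What to change.** Reconcile the passages by moving the randomisation step. In sections 1.2, 4.1 and 7.4, and in note h of Tables 1.3-1 and 7.5-1, state that registration and randomisation in REDCap take place only once screening is complete and the first infusion is scheduled, and no earlier than the calendar day before that infusion (Day 0 and Day 1, as the tables show). Carry the same sentence to the text under Figure 4.1-1. Leave the 3-day and 4-day limits from consent, and the treatment itself, as they are.

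The cost is one sentence in the Protocol and in the site instructions. The small downside is that sites learn the arm at most about a day ahead; this looks workable, because section 6.3.1 has the study drugs stored in each institution's pharmacy.

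The change reduces the loss without removing it. A scheduled infusion can still slip, and undosed women would remain outside observation under section 10.1 and outside the FAS under section 14.1 unless those sections are also revised.

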### 1.3 STUDY SCHEDULE

The study will be conducted according to the following table

**Table 1.3-1 Schedule of data collection and monitoring for participant (mother and fetus)**

| Period                                                               | Screening period a |                       | Observation period during pregnancy b |                                       |                            |                            |                            |                            |                            |                                          | Observation period after the termination of pregnancy  |                                                    | At the cancellation of the participation in the trial d | Follow-up observation after the cancellation of participation in the trial e |
|----------------------------------------------------------------------|-------------------------------|-----------------------|--------------------------------------------------|---------------------------------------|----------------------------|----------------------------|----------------------------|----------------------------|----------------------------|------------------------------------------|--------------------------------------------------------|----------------------------------------------------|--------------------------------------------------------------------|-----------------------------------------------------------------------------------------|
| Working item                                                         | Screening period Days -3 to 0 | Registration on Day 0 | Week 1 Day 1                                     | Week 2 Day 8 $\pm$ 2 day  | Week 3 Day 15 $\pm$ 2 days | Week 4 Day 22 $\pm$ 2 days | Week 5 Day 29 $\pm$ 2 days | Week 6 Day 36 $\pm$ 2 days | Week 7 Day 43 $\pm$ 2 days | Week 8~ c Day 50 $\pm$ 2 days | At the termination of pregnancy (delivery) $\pm$ 1 day | At examination for maternal discharge $\pm$ 2 days |                                                                    |                                                                                         |
| Obtaining consent f                                       | X                             |                       |                                                  |                                       |                            |                            |                            |                            |                            |                                          |                                                        |                                                    |                                                                    |                                                                                         |
| Participant: background information · body weight                    | X o                |                       |                                                  |                                       |                            |                            |                            |                            |                            |                                          |                                                        |                                                    |                                                                    |                                                                                         |
| Registration · randomization                                         |                               | X                     |                                                  |                                       |                            |                            |                            |                            |                            |                                          |                                                        |                                                    |                                                                    |                                                                                         |
| Care in hospital g                                        |                               |                       | X                                                | X                                     | X                          | X                          | X                          | X                          | X                          | X                                        | X                                                      | X                                                  |                                                                    |                                                                                         |
| Protocol treatment h                                      |                               |                       | X                                                | X                                     |                            |                            |                            |                            |                            |                                          |                                                        |                                                    |                                                                    |                                                                                         |
| Physical findings i                                       | X                             |                       | X                                                | X                                     | X                          | X                          | X                          | X                          | X                          | X                                        | X                                                      | X                                                  | X                                                                  |                                                                                         |
| Vital signs (blood pressure · pulse · body temperature) i | X                             |                       | X                                                | X                                     | X                          | X                          | X                          | X                          | X                          | X                                        | X                                                      | X                                                  | X                                                                  |                                                                                         |
| Hematological examination i                               | X p                |                       |                                                  | X                                     | X                          | X                          | X                          | X                          | X                          | X                                        | X                                                      | X                                                  | X                                                                  |                                                                                         |
| Blood biochemical test i                                  | X p                |                       |                                                  | X                                     | X                          | X                          | X                          | X                          | X                          | X                                        | X                                                      | X                                                  | X                                                                  |                                                                                         |
| Urinalysis (Qualitative: protein · sugar) i               | X p                |                       |                                                  | X                                     | X                          | X                          | X                          | X                          | X                          | X                                        | X                                                      | X                                                  | X                                                                  |                                                                                         |
| ECG                                                                  | X p                |                       |                                                  |                                       |                            |                            |                            |                            |                            |                                          |                                                        |                                                    |                                                                    |                                                                                         |

|                                                                                 |                |  |                |                |   |   |   |   |   |   |   |   |   |   |
|---------------------------------------------------------------------------------|----------------|--|----------------|----------------|---|---|---|---|---|---|---|---|---|---|
| Culture of vaginal microorganisms (each institute) i                 |                |  | X r | X s | X | X | X | X | X | X | X |   |   |   |
| Culture of vaginal Ureaplasma spp. j                          |                |  | X r | X s |   |   |   |   |   |   |   |   |   |   |
| PCR for vaginal Ureaplasma spp. j                             |                |  | X r | X s |   |   |   |   |   |   |   |   |   |   |
| Culture of Ureaplasma spp. on the surface of the placenta j   |                |  |                |                |   |   |   |   |   |   | X |   |   |   |
| PCR for Ureaplasma spp. on the surface of the placenta j      |                |  |                |                |   |   |   |   |   |   | X |   |   |   |
| Histological examination for placenta                                           |                |  |                |                |   |   |   |   |   |   | X |   |   |   |
| Estimated fetal weight i                                             | X a |  |                | X              | X | X | X | X | X | X |   |   |   |   |
| Fetal ultrasonography (Doppler · amniotic fluid volume estimation) i | X a |  |                | X              | X | X | X | X | X | X |   |   |   |   |
| Confirmation of drug used concomitantly k                            | X              |  | X              | X              | X | X | X | X | X | X | X | X | X | X |
| Confirmation of adverse events l                                     |                |  | X              | X              | X | X | X | X | X | X | X | X | X | X |
| Survey for the reasons of the termination of pregnancy m             |                |  |                |                |   |   |   |   |   |   | X |   |   |   |
| Findings on delivery n                                               |                |  |                |                |   |   |   |   |   |   | X |   |   |   |

a. The maximum length of screening period is 3 days.

b. The planned interview, physical examination, ultrasonography, and sampling of biological specimens should be performed before the administration of test drugs. If the chief investigator (CI) or sub-investigator (SI) decides to terminate the pregnancy before the completion of protocol treatment, he/she should finish protocol treatment at the time of the decision, and will transfer to the observation period after the termination of pregnancy.

c. After week 8, CI or SI should perform the planned interview, physical examination, ultrasonography, and sampling of biological specimens once a week until the day of the termination of pregnancy.

d. CI or SI should perform the physical examination, sampling of biological specimens, and confirmation of drugs used concomitantly and adverse events within 3 days after the cancelation of participation in the trial.

e. CI or SI should perform follow-up observation after the cancelation of participation in the trial at the one-month postpartum medical examination.

f. CI or SI must obtain consent before starting examination during the screening period.

g. CI or SI should care for patients in hospital at least for the period from the start of protocol treatment to 3 days after delivery.

- h. CI or SI must start protocol treatment within 4 days after obtaining consent.
- i. CI or SI should examine the estimated fetal weight once a week at or after Week 3, until the decision to terminate the pregnancy. However, the hematological examination and blood biochemical test should be performed only when needed at or after Week 4, until the decision to terminate the pregnancy.
- j. CI or SI should not take biological specimens from patients if the patients become complicated with COVID-19 infection. In addition, all preserved specimens should be abandoned.
- k. If CI or SI decides to cancel participation in the trial due to the adverse events, CI or SI should continue the investigation of adverse events due to the test drugs or drugs used concomitantly which are the reasons for the cancelation of participation in the trial, from the cancelation to the one-month postpartum medical examination.
- l. CI or SI should investigate the occurrence of adverse events in the subject (mother and fetus). As for the mother, CI or SI should investigate from the starting day of protocol treatment to the observation period after the termination of pregnancy (or day of cancelation of participation in the trial). As for the fetus, CI or SI should investigate from the starting day of protocol treatment to the termination of pregnancy (or day of cancelation of participation in the trial). However, if CI or SI decides to cancel participation in the trial due to the appearance of adverse events, CI or SI should continue the investigation of adverse events due to the test drugs or drugs used concomitantly which are the reasons for the cancelation of participation in the trial, from the cancelation to the one-month postpartum medical examination.
- m. CI or SI should investigate the decision day of the termination of pregnancy, the time (day, hour, minute) of delivery, the reasons for termination of the pregnancy (both maternal and fetal causes).
- n. CI or SI should investigate the delivery mode, presence/absence of stillbirth and the day of stillbirth, placental weight, and presence/absence of placental infarction.
- o. CI or SI can use the data for body weight which is measured and recorded appropriately within 14 days before obtaining consent instead of body weight during screening period.
- p. CI or SI can use the data for hematological examination, blood biochemical test, urinalysis, and ECG, which are measured and recorded appropriately within 3 days before obtaining consent instead of those during screening period.
- q. CI or SI can use the data for estimated fetal weight, and fetal ultrasound (amniotic fluid volume estimation), which are measured and recorded appropriately within 7 days before obtaining consent instead of those during screening period.
- r. The sampling of vaginal flora should be performed before the starting of protocol treatment. It is possible to perform it during the screening period.
- s. CI or SI should perform the sampling of vaginal flora for the culture of *Ureaplasma* spp. or PCR of *Ureaplasma* spp. on Day 8  $\pm$  2 days. However, if CI or SI finishes the protocol treatment before Day 8, CI or SI should not perform these samplings.

<Table 1.3-2 Schedule of children?

